### **9.1.3 Tertiary study outcome parameters**

- Glycometabolic state (fasting blood glucose, HbA1c, insulin, GLP-1, DPP-4), inflammatory state (CRP, high-sensitivity CRP, TNF-alpha, etc), renal function (hemoglobin, hematocrit, urinary albumin excretion, creatinin, urea, sMDRD), lipid and cholesterol spectrum (LDL, HDL, total cholesterol, triglycerides), levels of advanced glycation endproducts (AGEs) measured in blood and by skin autofluorescence, neurohormones (NT-proBNP, plasma renin activity, aldosterone, etc), and protein profiles (e.g. mRNA) will be determined before hospital discharge and at each outpatient clinic visit to investigate the relationship of these factors with the intervention. Furthermore, the impact of these factors on LVEF, cardiovascular endpoints, and heart failure will be determined.
- Infarct size, TEI, functional MRI, and local contractility will be determined using LGE CMR imaging at 4 months follow-up. The impact of infarct size and TEI on LVEF, cardiovascular endpoints, and heart failure will be determined.
- The presence of pathologic Q waves on the ECG will be monitored before hospital discharge and at each outpatient clinic visit.
- Echocardiographic parameters of systolic and diastolic function, and valvular functions during hospitalization and at 4 months follow-up.
- Body Mass Index will be measured before hospital discharge and at each outpatient clinic visit.

- Safety and serious adverse event monitoring, i.e. the prevalence of lactic acidosis and worsening renal failure will be monitored during hospital admission, before hospital discharge and at each outpatient clinic visit.

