## 5. STUDY POPULATION

### 5.1 Population

All patients with an acute STEMI admitted to the University Medical Center of Groningen who are amenable to PCI are considered for participation in the study. During the PCI procedure, patients will be asked for their verbal informed consent by the treating cardiologist and catheterization laboratory nurse (independent witness). Patients will receive the study drug as soon as possible after PCI, but at least within 3 hours after PCI. Prior to administration of the first gift, the nurse at the CCU administering the first dose will verify if patients still want to participate, and the patient information letter is handed over to the patient. Time of treatment will be recorded by the CCU nurse and verified by the investigator. In a later stadium following the PCI procedure, patients will sign the written informed consent.

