### **7.2 PCI procedure**

All patients will be transported to the catheterization laboratory as soon as possible after admission to the hospital. At admission blood will be drawn from the patient by vena puncture for standard lab analysis. After gaining arterial access at the catheterization laboratory, both coronary arteries will be visualized. If the coronary anatomy of the culprit lesion is suitable for percutaneous intervention, PCI will be performed. Primary treatment of the ischemia related coronary artery will consist of thrombus aspiration followed by stent implantation (at least one stent sized  $\geq 3.0\text{mm}$ ). Additional balloon angioplasty will be performed when necessary. Thrombus aspiration will be performed using an aspiration device (CE, Medtronic Corporation, Santa Rosa, California, USA).

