### **9.3.5 Skin autofluorescence**

Tissue AGE accumulation was assessed using a validated skin autofluorescence (AF) reader (advanced glycation end-products reader; patent PCT/NL99/00607;DiagnOptics BV, Groningen, The Netherlands). The AGE-reader illuminates a skin surface of approximately 2 cm^2, guarded against surrounding light, with an excitation light source between 300-420 nm (peak excitation ~370 nm). Light from the skin is measured with a spectrometer in the 420-600 nm range, using 200 µm glass fibers. The value of skin AF is calculated as the ratio of the light intensity in the 420-600 nm wavelength range and the light intensity in the 300-420 nm wavelength range. Meerwaldt et al have shown that repeated skin AF measurements on one day show an overall Altman error rate of 5.03% [78]. Intraindividual seasonal variance shows an Altman error rate of 5.87% [78]. The difference between repeated measurements does not alter depending on skin AF level [78]. Skin AF will be measured at the volar side of the lower arm at approximately 10 to 15 cm below the elbow fold. The measurement was performed three times at a healthy skin site (i.e. without visible vessels, scars or other skin abnormalities) and an average was calculated. Skin AF will be measured during hospitalization, and 4 months after randomization.

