#### 9.4 Study visits

The study visits are summarized in the study flow chart (chapter 4, page 21). All efforts will be made to perform study visits as scheduled. However, a 5-day margin will be allowed for visits T1 and T2, and a 10-day margin will be allowed for visits T3, T4 and T5. All study procedures will have to be performed during study visit as scheduled, with the exception of the CMR-scan. The CMR-scan may be performed 10 days before visit T3.

- During hospitalization (T0)
  - inclusion/exclusion;
  - primary PCI (see inclusion criteria);
  - verbal followed by written informed consent;
  - randomization;
  - dispense study drug;
  - NYHA heart failure score (see appendix, chapter 14)
  - medical history;
  - concomitant medication;
  - ECG;
  - echocardiography (diastolic function);
  - skin autofluorescence;
  - serious adverse events recording;
  - clinical examination (blood pressure, heart rate, length, weight,);

- laboratory analysis (pregnancy test for female patients of childbearing potential, regular hematology and biochemistry, plus glycometabolic state, inflammatory state, lipid and cholesterol spectrum, AGEs, renal function, and neurohormones);
- oral glucose tolerance test (OGTT);
- Visit 1 (T1) at 2 weeks:
  - concomitant medication;
  - NYHA heart failure score;
  - ECG;
  - serious adverse events recording;
  - clinical examination (blood pressure, heart rate, length, weight,);
  - laboratory analysis (pregnancy test for female patients of childbearing potential, regular hematology and biochemistry, plus glycometabolic state, inflammatory state, lipid and cholesterol spectrum, AGEs, renal function, and neurohormones).
- Visit 2 (T2) at 6-8 weeks:
  - concomitant medication;
  - dispense study medication;
  - NYHA heart failure score;
  - ECG;
  - serious adverse events recording;
  - clinical examination (blood pressure, heart rate, length, weight,);
  - laboratory analysis (pregnancy test for female patients of childbearing potential, regular hematology and biochemistry, plus glycometabolic state, inflammatory state, lipid and cholesterol spectrum, AGEs, renal function, and neurohormones).

- Visit 3 (T3) at 4 months:
  - concomitant medication;
  - stop study medication and record the amount of study drug received, dispensed, consumed or administered for drug accountability;
  - NYHA heart failure score;
  - ECG;
  - echocardiography (diastolic function);
  - skin autofluorescence;
  - CMR-scan (primary endpoint);

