## **11. STATISTICAL ANALYSIS AND SAMPLE SIZE**

### **11.1 Statistical analysis**

Analyses will be performed according to the intention-to-treat principle for the whole population and in the specified subgroups. An analysis per protocol will also be performed. Differences between group means will be assessed with the two-tailed Student's t-test. Chi-square analysis or Fisher's exact test is used to test differences between proportions. Survival will be calculated by the Kaplan-Meier product-limit method. The Mantel-Cox (or log-rank) test will be used to evaluate differences in survival between the two treatment groups. The Cox proportional-hazards regression model will be used to calculate relative risks and to adjust for differences in baseline characteristics. The relationship between metformin use and the primary and secondary endpoints will be studied using linear regression analysis, in which the outcome at the time of determination will be adjusted for the outcome at baseline. In addition, to assess the relationship between the determinant and the outcome over multiple measurements in time, GEE (generalized estimation equations) will be used as a method for dealing with correlated data arising from repeated measurements. Statistical significance is considered as a two-tailed p value <0.05. The Statistical Package for the Social Sciences (SPSS Inc., Chicago, IL, USA) version 16.0 will be used for all statistical analysis.

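### Section 11.1 adjusts for a baseline that is not fixed as pre-dose, while the schedule points to, or allows, post-dose first values for the study markers, echo and skin autofluorescence

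*Protocol*

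**What the plan says.** Section 5.1 fixes the start of treatment: "Patients will receive the study drug as soon as possible after PCI, but at least within 3 hours after PCI".

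The first values of the serial measures are placed as follows.

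- Section 9.1.3: the glycometabolic, inflammatory, renal, lipid, AGE and neurohormonal markers "will be determined before hospital discharge and at each outpatient clinic visit to investigate the relationship of these factors with the intervention".
- Section 9.1.3: "Echocardiographic parameters of systolic and diastolic function, and valvular functions during hospitalization and at 4 months follow-up".
- Section 9.3.5: "Skin AF will be measured during hospitalization, and 4 months after randomization".
- Section 9.4 puts randomisation, drug dispensing, laboratory panel, echo, skin autofluorescence and OGTT in one visit, T0, which covers the whole admission. It gives no order or clock time.

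Section 11.1 studies the relation of metformin to the primary and secondary endpoints by "linear regression analysis, in which the outcome at the time of determination will be adjusted for the outcome at baseline". It adds GEE for repeated measurements and also plans a two-tailed t-test. It does not say what baseline is.

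Two blood measurements clearly precede treatment: the creatinine used for eligibility (section 5.3, before PCI) and the draw in section 7.2, "At admission blood will be drawn from the patient by vena puncture for standard lab analysis". Section 9.3.4 separates such standard tests from the additional ones, which include glycometabolic and inflammatory markers and markers of heart failure.

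**The concern.** A baseline covariate is harmless, and usually gains precision, because randomisation makes it independent of treatment. That protection ends with the first dose. If the in-hospital value is entered as baseline, the model conditions on something the drug may already have moved, and part of the effect under study can be credited to the covariate. The GEE analysis has the same weakness if T0 is handled as a pre-treatment time point.

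The outcomes at stake are those meant to show how metformin acts: glycometabolic and inflammatory markers, NT-proBNP, and echo function. The protocol's own rationale does not let an early effect be ruled out. Section 1 cites experimental work in which a single dose raised myocardial AMPK activity and reduced infarct size, and in which dosing at reperfusion was protective.

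**Working it through.** **Timing.** The protocol treats the period before discharge as a sampling point of its own. Section 9.3.3 lists ECGs at presentation, after PCI, before discharge and at outpatient visits as separate occasions. The safety item in section 9.1.3 separates monitoring during admission from monitoring before discharge. Set against dosing within 3 hours of PCI:

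| Measure | First scheduled value | Relative to first dose |
|---|---|---|
| Fasting glucose, insulin, HOMA-IR, OGTT | In hospital; OGTT read at 120 minutes (section 14.2) | In practice after (inference: emergency patients, dosed within 3 hours of PCI) |
| Other study markers | Before discharge | Schedule points to after |
| Echo, skin autofluorescence | During hospitalisation | Open; after is allowed |
| Creatinine, sMDRD | Pre-PCI creatinine (section 5.3) | Before |
| LVEF by CMR | 4 months only (section 9.3.6) | No baseline scan |

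**Reach of the model.** CMR LVEF has no baseline scan and clinical events have no baseline value, so the adjustment sentence can work mainly for the serial measures. Section 9.1.3 calls these tertiary, but section 2.2 lists the laboratory markers and echo as secondary objectives, and section 11.1 covers secondary endpoints.

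**Bias.** Let τ be the effect at follow-up, δ0 the effect already present in the value used as baseline, and β the within-arm slope of follow-up on that value. The adjusted treatment coefficient is

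(difference in follow-up means) − β × (difference in baseline means),

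with expectation τ − β·δ0. Writing δ0 = f·τ gives τ(1 − β·f), so the share lost is β·f.

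**Size.** The protocol states no figure for these analyses. Its sample size, (1.96 + 0.84)² × 2 × 9²/3² = 141.12 per arm, reproduces but concerns LVEF and has no bearing here. Both β and f are therefore assumptions:

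| f (share of effect present at sampling) | β = 0.3 | β = 0.5 | β = 0.7 |
|---|---|---|---|
| 0 | 0% | 0% | 0% |
| 0.10 | 3% | 5% | 7% |
| 0.25 | 7.5% | 12.5% | 17.5% |
| 0.50 | 15% | 25% | 35% |

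**Simulation check.** The settings were 190 per arm (380/2), equal variances, an illustrative effect of 3/9 = 0.33 SD and 3,000 replicates.

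- True pre-dose baseline: the mean estimate was 1.00 of the truth at all three slopes.
- f = 0.5: it was 0.857, 0.745 and 0.655 of the truth for slopes 0.3, 0.5 and 0.7, against 0.85, 0.75 and 0.65 from the formula.
- Power at slope 0.5: about 97% with a true baseline, about 92% at f = 0.25 and about 80% at f = 0.5. The unadjusted comparison had about 90%. Adjustment can therefore do worse than none, but only when the early effect is substantial.

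**The case against.** The strongest reply is that the protocol leaves the matter open rather than deciding it wrongly. Baseline is undefined, T0 has no internal order, and discharge may be read as only an outer limit for sampling. The flow chart and the laboratory overview, which could hold draw times, are not available for review, and the definition of an analysis baseline is often left to a SAP.

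Part of this stands. A reader might infer that every in-hospital value is post-dose and is the baseline the sponsor will use. The text does not say so: echo and skin autofluorescence could precede the first dose, and creatinine has a pre-PCI value. A reader might also infer a known and large loss, such as 50 to 70%. That would need the whole 4-month effect to be present before discharge (f = 1, slopes 0.5 to 0.7), and nothing in the protocol supports it. For a marker that has barely moved by discharge, the loss is near zero.

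The outer-limit reading fits poorly with sections 9.3.3 and 9.1.3, where before discharge is listed beside other in-hospital occasions. Nor is this only SAP detail. Section 11.1 already commits to the adjustment, the sampling schedule belongs to the protocol, and no SAP can recover a pre-dose marker that was never drawn.

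**Conclusion.** The point holds in limited form. As written, section 11.1 lets a post-dose value serve as the baseline covariate. The schedule makes that practically certain for fasting and OGTT measures, likely for the other study markers, and possible for echo and skin autofluorescence.

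The adjusted estimate is then biased by −β·δ0. Under the assumed ranges (slope 0.3 to 0.7, f from 0.1 to 0.5, equal variances) this removes about 3 to 35% of the effect. The direction is toward zero only if early and late effects share a sign. The figures illustrate the mechanism and do not predict the loss in this trial.

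The 4-month CMR LVEF endpoint, the unadjusted t-test and outcomes with a pre-PCI value are untouched. The issue therefore bears on secondary and tertiary findings, not on the main conclusion.

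**What to change.** - In section 11.1, define baseline as the last value before the first dose.
- Where no pre-dose value exists, treat the in-hospital value as a post-randomisation measurement in both the regression and the GEE, and do not enter it as a covariate. Report the unadjusted comparison, or adjust only for pre-randomisation characteristics already collected.
- Record sampling time relative to the first dose for laboratory values, echo, skin autofluorescence and OGTT. Section 9.3.4.1 already records enzyme sampling in minutes after randomisation, so the practice is familiar to the trial.

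The cost is a definition, a time field in the eCRF, and some precision for the affected outcomes. In the illustration at slope 0.5, the unadjusted test has about 90% power, against about 97% if a genuine pre-dose covariate existed.

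Running the study markers on the admission blood is optional and not a like-for-like substitute. That draw precedes the verbal consent sought during PCI (section 5.1), so its use depends on consent. It is also not a fasting sample, and section 1 notes that raised admission glucose may reflect physical stress.

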**Outcome measures:** Primary endpoint measure is the difference in left ventricular ejection fraction between both groups as determined by cardiac magnetic resonance imaging (CMR) 4 months after randomization. Secondary outcome measures are clinical outcome – mortality, re-intervention, recurrent MI, hospitalization for heart failure – and myocardial infarct size measured with LGE CMR-imaging. In addition, the impact of metformin on new-onset diabetes, glycometabolic parameters, neurohormones and advanced glycation endproduct levels will be evaluated. Finally, safety of metformin therapy will be assessed with emphasis on metformin-associated lactic acidosis (MALA) and renal function.

**Expected results:** We hypothesize that treatment with metformin will prevent adverse left ventricle (LV) remodeling after MI. This will result in preserved LV function (assessed by CMR), and a lower rate of heart failure hospitalizations and mortality.

Keywords: acute myocardial infarction, heart failure, left ventricular ejection fraction, magnetic resonance imaging, metformin, diabetes

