#### **8.4 Summary of known and potential risks and benefits**

The possible occurrence of a severe lactic acidosis is known as one of the adverse effects of metformin. In contrast with the huge number of treated patients, metformin-associated lactic acidosis (MALA) is rare, with an estimated incidence of three per 100,000 metformin-treated patients per year, but is associated with a high mortality rate, averaging 50% (21;22). In most cases, MALA occurs in a previously treated type 2 diabetic patient when a concurrent disease induces an acute renal failure leading to metformin accumulation. The association between metformin and decreased renal perfusion in MALA lead to the contraindication of metformin in patients with heart failure and decreased renal failure. The causative mechanism has been disputed by Lalau et al (2001) (23).

According to current guidelines metformin therapy is contraindicated in patients with acidosis, renal insufficiency or heart failure with NYHA classification II or higher ([www.fk.cvz.nl](http://www.fk.cvz.nl)).

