### **8.5 Description and justification of route of administration and dosage**

The route of administration of the metformin 500 mg 2dd1 tablets is oral. The bioavailability is approximately 50 to 60 %. Withdrawal of study drug can be considered if the study drug is not tolerated or otherwise indicated in a specific patient (see withdrawal criteria). No other modifications to study drug can be made.

Normal starting dosage of metformin for treatment of diabetes type II varies from 500mg once daily to 500mg twice daily. Maximum dosage of metformin for treatment of diabetes type II is 3000mg divided over 3 gifts. In our study protocol we chose a dose of 500mg administered twice daily. Based on figures from the EASD 2009 guidelines (3) metformin leads to side effects, most all gastrointestinal discomfort, in 30% of patients and results in discontinuation of 2-5% of patients started on metformin therapy. The side effects are, equal to the antihyperglycaemic effects, dose-dependent. Since the time window of administration of metformin is relatively short (4 months) for titration, metformin will be dosed in one uniform dosage. Most importantly, there is no evidence for a dose-dependent relation between metformin and the supposed cardioprotective effects. The dosage of metformin administered in the animal experiments (34-36) was high (metformin 250mg/kg/ml) compared to dosages normally administered in humans (8-45mg/kg/day). However, animal experiments demonstrated that relatively high dosages of metformin were necessary for the drug to exert its antihyperglycaemic effects in hyperglycaemic rats. Therefore, it might be deducted that the non-dose-dependent cardioprotective effects of metformin show at a dosage of 500mg metformin twice daily.

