### 10.3 Adverse and serious adverse events

Adverse events are defined as any undesirable experience occurring to a subject during a clinical trial, whether or not considered related to the investigational procedure. All adverse events reported spontaneously by the subject or observed by the investigator or his staff will be recorded. Disease related adverse events, which are clearly related to the underlying condition of the patient and are not related to the intervention, will only be reported 6 monthly to the METC.

A serious adverse event is any untoward medical occurrence or effect that:

- results in death;
- is life threatening (at the time of the event);
- requires hospitalization or prolongation of existing inpatients' hospitalization;
- results in persistent or significant disability or incapacity;
- is a new event of the trial likely to affect the safety of the subjects, such as an unexpected outcome.

Since metformin is a widely used medicine which adverse effects have been described in detail, serious adverse events which are common in patients suffering from myocardial infarction which have no known association with the intervention ("disease related adverse events") will be reported 6 monthly to the METC. All serious adverse events with a known association with metformin will be reported to the accredited METC that approved the protocol, according to the requirements of that METC. Serious adverse events that are used to assess safety by the DSMB, which include death, re-MI, target vessel revascularization, worsening renal failure and lactic acidosis will be reported to the METC at all times.

Subjects transferred to other hospitals (referring hospitals) after PCI, which is standard care, will not be considered as an SAE. For logistical reasons, the discharge date from the UMCG will be used to plan the subsequent study visits (T1 – T5). The actual dates that the patients are discharged from the referring hospitals will be collected afterwards and recorded in the database as date of discharge.

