#### 10.5 Data Safety Monitoring Board

A DSMB is established to perform ongoing safety surveillance and to perform interim analyses on the safety data. This committee is an independent committee, consisting of:

- [name], PhD, epidemiologist (Chair);
- [name], MD PhD, Interventional cardiologist (member);
- [name], MD PhD, Cardiologist (member);
- [name], MD, hospital pharmacist, epidemiologist (member);
- [name], MD, endocrinologist (member).

These members have no conflict of interest with the sponsors of the study. The DSMB will meet on regular basis (i.e. 2-3 times per year) to evaluate (serious) adverse events, drug safety and clinical endpoints. The charter of the DSMB is added as an attachment (see attachments).

Extending recruitment (based on actual control arm response rates being different to predicted rather than on emerging differences) will be recommended by the DSMB based on the conditional power analysis that will be performed after 280 patient have reached their primary endpoint (LVEF analysis by CMR imaging 4 months after randomization) based on actual control arm response rates being different to predicted rather than on emerging differences. The maximal number of patients to which the inclusion can be extended in this trial will be limited to 450.

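### Sections 9.1.3, 9.4 and 10.3 disagree on which adverse events are collected, and the side effects the protocol calls common have no uniform collection and no named outcome (minor)

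*Protocol*

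**What the plan says.** The protocol speaks to safety data in several places.

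- **Outcome (9.1.3).** The tertiary safety outcome reads "Safety and serious adverse event monitoring, i.e. the prevalence of lactic acidosis and worsening renal failure will be monitored during hospital admission", with the same monitoring before discharge and at each outpatient visit. The abbreviation introducing the two conditions makes them the definition, not examples.
- **Visit schedule (9.4).** Each list, T0 to T5, carries the item "serious adverse events recording". None has an item for non-serious events or tolerability.
- **General rule (10.3).** "All adverse events reported spontaneously by the subject or observed by the investigator or his staff will be recorded", whether serious or not. The same section lists the serious events that the DSMB uses to assess safety: death, re-infarction, target vessel revascularisation, worsening renal failure and lactic acidosis.
- **Summary.** "safety of metformin therapy will be assessed with emphasis on metformin-associated lactic acidosis (MALA) and renal function", which sets a priority but excludes nothing.
- **DSMB (10.5).** The board meets two to three times a year "to evaluate (serious) adverse events, drug safety and clinical endpoints".
- **Expected harm (8.5).** Citing a guideline, the protocol says that "metformin leads to side effects, most all gastrointestinal discomfort, in 30% of patients and results in discontinuation of 2-5% of patients" started on the drug, and adds that these effects depend on dose.
- **Analysis (11.1).** "Chi-square analysis or Fisher's exact test is used to test differences between proportions", without reference to any particular outcome.

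**The concern.** Read together, these sections give staff two different instructions. Someone working from the 9.4 list records serious events. Someone working from 10.3 records whatever the patient mentions or the staff notice. Gastrointestinal discomfort will seldom meet the seriousness definition in 10.3, so its capture depends on which section is followed and on whether the patient brings it up. The outcome in 9.1.3 is narrower still and omits the harm that 8.5 describes as common.

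Two things are at stake.

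- **Benefit and harm.** Patients with diabetes are excluded (5.3), so those enrolled have no established diabetes for which they would otherwise take the drug. Tolerability is then part of judging whether any gain in ejection fraction is worthwhile. A safety report confined to the two named conditions could be taken as evidence of good tolerability when tolerability had not been measured in a uniform way.
- **Reading the per-protocol analysis.** Symptoms can end protocol therapy (9.5.1), compliance means more than 80% of drug used (8.9), and the per-protocol analysis keeps compliant patients only (9.2). If side effects led to more stopping on metformin, that analysis would be selected differently by arm, and unevenly collected events would not explain why.

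**Working it through.** **Inputs**
- Number randomised: 63 × 6 + 2 = 380 (6.1), so 190 per arm, assuming equal arms.
- Treatment period: 4 months (7.4).
- Lactic acidosis: "an estimated incidence of three per 100,000 metformin-treated patients per year" (8.4).
- Side effects 30%, discontinuation 2-5% (8.5).
- Side-effect rate on placebo: not in the document, so assumed over a range.

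**The plan's own figures.** The protocol states no sample size or power for any safety comparison. Its primary calculation (11.3.1) reproduces: (1.96 + 0.84)² × 2 × 9²/3² = 7.84 × 18 = 141.12 per group, or 282 in total. Allowing for 26% without a scan, 282/0.74 = 381.1, close to the stated 380. This serves only to confirm the arm size.

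**Lactic acidosis.** 190 × (3/100,000) × (4/12) = 0.0019 expected cases on metformin. The chance of at least one is 1 − (1 − 0.00001)^190 = 0.0019, about 0.2%. This outcome cannot separate the arms. For worsening renal failure the protocol gives no rate, so no count can be worked out.

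**Common side effects, if the 8.5 figures applied here**
- Side effects: 0.30 × 190 = 57 metformin patients.
- Discontinuation: 0.02 × 190 = 3.8 to 0.05 × 190 = 9.5 metformin patients.

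**Power for a comparison of side effects, 190 per arm, two-sided 5%.** With d = p₁ − p₂ and p̄ the mean of the two rates,

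power = Φ{ [d − 1.96·√(2p̄(1 − p̄)/190)] / √[(p₁(1 − p₁) + p₂(1 − p₂))/190] }

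For 30% against 20%: (0.100 − 1.96 × 0.04443)/0.04413 = 0.293, and Φ(0.293) = 0.615.

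| Assumed placebo rate | Power | 95% CI half-width for the risk difference |
|---|---|---|
| 10% | 99.9% | 7.8 points |
| 15% | 94.1% | 8.3 points |
| 20% | 61.5% | 8.6 points |
| 25% | 19.2% | 9.0 points |

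**Effect of incomplete capture.** Suppose, as an assumption, that unsolicited reporting catches half of the events in both arms. True rates of 30% and 10% would then be seen as 15% and 5%, and power falls from 99.9% to 90.4%. True rates of 30% and 20% would be seen as 15% and 10%, and power falls from 61.5% to 31.3%.

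**The sections side by side**

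| Section | Events covered | How found |
|---|---|---|
| 10.3 | all adverse events | volunteered or observed |
| 9.4 | serious events only | item at each visit |
| 9.1.3 | lactic acidosis, worsening renal failure | monitored in hospital and at visits |

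Gastrointestinal events fall under the first row only, and no section names them, or stopping for adverse events, as an outcome.

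**The case against.** A reader might infer that the common harm goes unrecorded, or that it has no comparison between the arms. The document does not support either reading. Section 10.3 requires non-serious events to be recorded when reported or observed, and 9.3.4.2 records newly found diabetes or prediabetes as an adverse event, so the protocol does use non-serious recording. The trial is randomised and double blind, and 11.1 supplies a test for proportions that could be applied to recorded events. Adverse-event tables are commonly left to the statistical analysis plan, which is not shown. The Summary and 10.5 describe safety more broadly than 9.1.3 does. The flow chart in section 4 is not reproduced, so what it lists is unknown.

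Discontinuation also leaves traces: symptoms as a withdrawal criterion (9.5.1), continued follow-up (9.5.3), tablet counts (8.8) and the compliance threshold (8.9).

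Nor can it be said that side effects are something this trial would measure well. The 30% is a guideline figure, 8.5 itself calls the effects dose-dependent, and the placebo rate is unknown; at 25% on placebo, power is only 19%.

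All of that stands. It does not remove the conflict between 9.4 and 10.3, and an analysis plan cannot recover events that were not asked about uniformly. It may also be said that relabelling the visit item would still leave reporting unsolicited. That is right, and it is why the fix includes a uniform question.

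**Conclusion.** The point holds as an inconsistency together with an outcome list that is too narrow. Sections 9.1.3, 9.4 and 10.3 give different scopes for safety data. The side effects that 8.5 describes as common may be recorded, but they have no scheduled uniform collection and are not a named outcome, and neither is stopping for adverse events. Of the two named outcomes, lactic acidosis has about 0.002 expected cases on metformin.

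This conclusion rests on the wording alone. The 57 patients with side effects and the 4 to 10 discontinuations assume that the figures in 8.5 carry over to this dose and to non-diabetic patients. The power range of 19% to 99.9% also depends on the assumed placebo rate. Severity is minor: the primary analysis is untouched and the remedy is wording.

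**What to change.** - **9.4.** At T1, T2 and T3, widen the item "serious adverse events recording" to cover all adverse events, serious and non-serious, asked in the same way of every patient. This brings the schedule into line with 10.3.
- **9.1.3.** Replace the closed list with one that names lactic acidosis, worsening renal failure, gastrointestinal adverse events and study-drug discontinuation for adverse events. Report each by arm as a risk difference with a 95% confidence interval, using the tests already in 11.1.
- **Power.** If power is quoted for side effects, give it as a range over stated placebo rates.

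The cost is a few more eCRF entries and one safety table, at existing visits. No dose, treatment rule or visit timing changes.
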